**Fig. 1 Fig1:**
[figure not shown]
Flow chart of the IDEAL trial *Defunctioning ileostomy, CR: continuity restoration

The list of randomization will be established before the implementation of the study with a 1:1 allocation ratio. It will be elaborated under the responsibility of the Clinical Research Platform, Assistance Publique – Hôpitaux de Marseille (APHM). A computer-generated randomized list will be drawn up using a permuted block design. Two stratification indicators will be retained: the center and the body mass index (< or ≥ 25 kg/m^2^).

This trial is supported by a grant from the French Ministry of Health (PHRC-18_0764).

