### Participating centers

The recruitment will be performed in 15 French public academic teaching hospitals. All participating sites will sign a convention with the Direction of Research and Clinical Innovation of APHM for ethical approval before beginning patient inclusion. All these centers are tertiary expert units in IBD, as it has been demonstrated that IPAA should be performed in mid- to high-volume centers, namely, those that perform at least 3 IPAA procedures per year [17].

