#### Statistical analysis

A sample size calculation will be performed on the hypothesis formulated on the primary endpoint, i.e., the overall morbidity, assessed 6 months post-randomization. Based on previous reports, the overall 6-month morbidity rate is 30% in the case of no ileostomy creation (i.e., experimental group) vs. 55% otherwise (control group) [6–8, 11–13]. With the alpha risk and power fixed to 0.05 and 0.80, respectively, 88 patients need to be included in each group, or 176 in total [Power Analysis and Sample Size Software Version 2008, Utah, USA]. Considering a drop-out rate of 10%, the objective is set to 194 patients.

The full analysis population (including all subjects who will be randomized and will at least be evaluated at baseline) will be used in the primary analysis, and the per-protocol population (including all subjects who will be randomized and will not have major protocol deviations) will be used in the secondary analysis to assess the robustness of the results. The demographic and baseline characteristics will be summarized for the 2 groups (‘control’ and ‘experimental’ groups). The scores of the QoL questionnaires will be calculated from the algorithm provided by the authors of the tools. No comparisons will be provided in accordance with the CONSORT guidelines.

The primary endpoint will be compared between the 2 groups (χ^2^ test or Fisher’s exact test) for the primary analysis. Logistic regression will be performed to adjust for potential confounding factors; variables relevant to the models will be selected based on their clinical interest and/or a threshold *p*-value ≤0.1 during univariate analysis. The final models will express the odd ratios and their 95% confidence intervals. The unadjusted analysis will be the primary analysis, and the adjusted analysis will be a complementary analysis. For the secondary endpoints, quantitative data will be compared using the Student’s t test or Mann-Whitney U test in accordance with the variable distribution, whereas qualitative data will be compared using χ^2^test or Fisher’s exact test, as appropriate.

For the analysis of overall survival, the last date of known contact will be used for subjects who have not died (the subjects will be considered censored). Overall survival will be estimated according to the Kaplan-Meier method. Comparisons between the 2 groups will be performed with the log rank test for the Kaplan-Meier estimates. Cox models will be created.

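### Randomisation is stratified by centre and BMI but the primary test uses neither factor: the test stays valid, is conservative if the strata matter, and is cheap to improve

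*Protocol article*

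**What the plan says.** In Methods and design (text after Fig. 1), the allocation list is "established before the implementation of the study with a 1:1 allocation ratio". The method is fixed: "A computer-generated randomized list will be drawn up using a permuted block design". So are the strata: "Two stratification indicators will be retained: the center and the body mass index", with BMI split at 25 kg/m². Under Participating centers: "The recruitment will be performed in 15 French public academic teaching hospitals". That makes 15 × 2 = 30 strata.

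Under Statistical analysis, "The primary endpoint will be compared between the 2 groups" by a chi-square or Fisher's exact test. A logistic regression follows, in which "variables relevant to the models will be selected based on their clinical interest and/or a threshold" of p ≤ 0.1 in univariate analysis; it reports odds ratios with 95% confidence intervals. The ranking is explicit: "The unadjusted analysis will be the primary analysis, and the adjusted analysis will be a complementary analysis". Nowhere does the article say that centre or BMI enters an analysis.

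**The concern.** Blocking within strata balances the arms on centre and BMI, so differences between strata largely drop out of the arm comparison. An unadjusted test still counts that between-stratum variation as noise. If morbidity differs by centre or BMI, the standard error is too large, the test rejects too rarely under the null, and some power is lost.

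Centre may well be prognostic. The Intervention section leaves approach, anastomosis type and drainage to each centre and requires only that they match across arms within a centre. BMI was chosen by the sponsor as a stratifier.

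The complementary model does not reliably close the gap. Its covariate rule does not name the two factors, and one route into the model is a p-value computed on the trial's own outcomes. What is at stake is some precision in the primary result and the reproducibility of the adjusted estimate.

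**Working it through.** **1. The plan's own sample size, and the power available.** Inputs from Statistical analysis: 30% against 55%, alpha 0.05, power 0.80, 88 per group. Pooled rate 0.425, two-sided:

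n = [1.960·√(2·0.425·0.575) + 0.842·√(0.30·0.70 + 0.55·0.45)]² / 0.25² = (1.370 + 0.569)² / 0.0625 = 60.2, so 61 per group, or 68 with continuity correction.

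The stated 88 does not follow from 80% power. It equals the continuity-corrected result for 90% power. That is a separate matter. Here it means that 88 per group gives 92.5% power with the chi-square test (90.9% with Fisher's exact test), so there is slack at the planned rates.

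**2. Why the unadjusted test is conservative.** Its variance uses p(1−p). Under balanced strata, the variance that matters is p(1−p) − V, where V is the between-stratum variance of the event rate. Approximately:

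type I error ≈ 2Φ(−1.960 / √(1 − V/[p(1−p)])).

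Read backwards, 4.0% corresponds to (1.960/2.054)² = 0.91, so about 9% of outcome variance lies between strata. A value of 3.1% corresponds to (1.960/2.157)² = 0.83, so about 17%.

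**3. Size by simulation.** From the documents: 176 patients, 15 centres, two BMI classes, 1:1 permuted blocks. Assumed, because the article gives no values: block size 4, unequal centre sizes, 40% of patients with BMI ≥ 25, between-centre SD 0 to 1.0 on the logit scale, BMI odds ratio 1 to 2. Overall rates were held at 55% and 30%. Each cell shows unadjusted chi-square / Cochran-Mantel-Haenszel (CMH) test over 30 strata / linear model with centre and BMI main effects, from 4,000 runs.

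| Centre SD, BMI OR | Type I error, % (common rate 42.5%) | Power, % |
|---|---|---|
| 0, 1 | 5.4 / 5.1 / 5.4 | 92.6 / 91.5 / 92.0 |
| 0.3, 1.5 | 4.8 / 4.9 / 4.9 | 92.6 / 91.9 / 92.7 |
| 0.5, 1.5 | 4.2 / 4.7 / 4.7 | 93.4 / 93.0 / 93.8 |
| 0.8, 2 | 3.7 / 4.8 / 4.8 | 93.8 / 94.7 / 95.1 |
| 1.0, 2 | 3.8 / 5.0 / 5.4 | 94.4 / 95.9 / 96.3 |

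Monte Carlo error is about √(0.05·0.95/4000) = 0.3 points for type I error and 0.4 points for power. With a common rate of 55%, the chi-square's type I error at SD 1.0 was 2.9%. A separate run with BMI OR 2 gave:
- SD 0.7: type I error 4.0%; power 93.3% (chi-square) against 93.6% (CMH).
- SD 1.0: type I error 3.1%; power 93.8% against 95.7%.

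**4. A smaller effect.** The 1992 randomised study in the Background found 52% against 32%, before closure morbidity. At those overall rates the stratified test gains about 1.5 to 3 points for SD 0.7 to 1.0; individual runs ranged from about 1 to 4.

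**5. Validity of the interval.** Coverage of the unadjusted 95% interval for the risk difference, simulated with no treatment effect, was 94.5% to 96.3% for SD 0.3 to 1.0.

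**6. The screening rule.** With 16 candidate covariates screened at p ≤ 0.1, the type I error for treatment was 4.5% to 4.9%, against 4.8% to 5.4% for a prespecified model. The mean number of covariates selected ran from 1.8 to 4.8, depending on how prognostic they were.

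**The case against.** The case for leaving the plan alone is substantial.

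- **The error is on the safe side.** A reader might infer that the primary p-value or interval is invalid. It is not: type I error stays at or below about 5% within simulation error, and coverage is close to nominal. This stands.
- **The gain is small and rests on assumed spread.** All centres are described as tertiary expert units. At SD 0.3 the chi-square matches or slightly beats CMH. A reader might find larger gains (81.3% against 85.3% at SD 1.0) by treating 55% and 30% as rates in an average centre. Adding spread then pulls the overall rates together, to about 54% and 33%, and so shrinks the effect. The protocol gives its figures as overall rates, so those gains do not apply to its scenario. This stands.
- **CMH over 30 strata is not free.** With 176/30 ≈ 6 patients per stratum and no prognostic strata, it loses about 1 point at 176 patients. At 122 patients, where power is near 80%, it gave 77.1% against 81.6%; the main-effects model gave 79.3%. This stands and shapes the fix.
- **The screen is half of an and/or rule and touches only a complementary model.** Centre and BMI could enter on clinical grounds, and a final covariate list may sit in an SAP that is not shown. A reader might infer that screening inflates false positives; the check shows that it does not. What remains is that the article itself states a rule that lets outcome data choose the model.
- **The odds ratio is the natural output of logistic regression.** At the planned rates it is (0.30/0.70)/(0.55/0.45) = 0.35, against a risk ratio of 0.30/0.55 = 0.55. Reporting a risk difference is easier to read, but this is largely preference.

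The mismatch itself is not answered by pointing to an unseen SAP, because the article fixes the unadjusted test as primary.

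**Conclusion.** The mismatch between stratified randomisation and unstratified primary analysis is real and stated. Its consequence is conservatism, not invalidity: type I error of about 3 to 4% instead of 5% if the centre SD is 0.7 to 1.0 on the logit scale and the BMI odds ratio is 2. The power forgone is about 0 to 2 points at overall rates of 55% and 30%, where power already exceeds 90%, and about 1.5 to 3 points at 52% and 32%. With weakly prognostic strata the sign reverses by about 1 point. All of these sizes depend on centre and BMI effects that the documents do not give. The screening rule is secondary: it leaves the adjusted estimate dependent on the data without inflating type I error. Minor, with moderate confidence: a cheap improvement.

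**What to change.** - **Primary endpoint.** Prespecify the comparison adjusted for BMI class and centre. Use a pooling rule for small centres fixed without sight of outcomes, or a logistic model with BMI class and a centre random intercept. Avoid relying on all 30 sparse strata.
- **Effect measure.** Report the adjusted risk difference with its 95% confidence interval, for example by standardising the fitted model over the trial population, beside the proportions in each arm.
- **Sensitivity analysis.** Keep the unadjusted chi-square test.
- **Complementary logistic model.** Force in centre and BMI. Replace the p ≤ 0.1 screen with a short fixed list from baseline data already in the eCRF, such as ASA score, smoking status, and corticosteroid or anti-TNF treatment. If the SAP already fixes such a list, this needs only a cross-reference.

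The cost is wording in the protocol and SAP, settled before outcome data are seen, with no extra patients or data. The statistical price is about 1 point of power at the planned size and rates if the strata turn out not to be prognostic, and more if power is nearer 80%.

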The secondary endpoints are as follows: 6-month major morbidity based on the Clavien-Dindo classification, [14] i.e., number of patients who develop at least one major complication at the 6-month follow-up; 6-month unplanned reoperation rate, i.e., any unplanned abdominal surgery, whether urgent or elective, other than ileostomy closure; 6-month anastomotic leakage rate assessed by a CT scan with an iodine injection, i.e., pelvic abscess, pelvic extradigestive air, pelvic free fluid or pelvic infiltration; 6-month mortality (linked or not with the disease); initial and cumulative 6-month length of hospital stay; 6-month unplanned readmission rate, i.e., other than for ileostomy closure; global and digestive quality of life (QoL) assessed by the Cleveland Global Quality of Life (CGQL) score [15] and the EuroQol Five-levels (EQ-5D-5 L) (i.e., utility values for health states) [16] at baseline and 3 and 12 months from continuity restoration (i.e., either IPAA or ileostomy closure); functional results assessed by the Cleveland Pouch Functional score (PFS) 3 and 12 months from continuity restoration [15]; 12-month pouch results: pouch failure (i.e., with definite ileostomy), anastomotic stricture, pouch in place, and repeat IPAA 12 months from continuity restoration; 12-month global morbidity (i.e., the number of patients who develop at least one complication 12 months from continuity restoration); and 12-month cost-utility analysis, performed 12 months from continuity restoration (cf. *‘* Economic assessment’ below). Though many redo-IPAAs are performed after one year, it is a secondary endpoint and it was felt not relevant enough in this trial to extend its follow-up.

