#### Data collection and monitoring

An electronic Case Report Form (eCRF) will collect the patients’ baseline data (sociodemographics, such as current age, age at UC diagnosis, sex, body mass index, weight gain since subtotal colectomy, ASA score, and smoking status; medical history, such as extent of UC, associated primary sclerosing cholangitis, and associated comorbidities; surgical history, such as indications for primary STC, delay between STC and IPAA, postoperative course of subtotal colectomy, and history of other surgical procedures; current and previous treatments, such as anti-TNF, immunosuppressive treatment, and corticosteroid therapy; and baseline QoL assessment, using CGQL and EQ-5D-5 L) as well as perioperative, short- and long-term data according to the abovementioned endpoints. Each patient will participate in the study for 15 months (as there are 12-month data collect points from continuity restoration, which is performed up to 3 months after IPAA in case of defunctioning ileostomy). Clinical reviews will be performed one and 6 months after IPAA and 3 and 12 months after continuity restoration (i.e., either IPAA or stoma closure).

Monitoring will be conducted to ensure that the data are accurate/complete, the safety and rights of subjects are being protected, and the study is conducted in accordance with the applicable regulatory requirements. No deidentified individual clinical trial participant-level data (IPD) will be shared. This monitoring (including data management and data quality insurance) will be ensured by the sponsor. The following monitoring will be conducted: informed consent, deviation of protocol, data collection, and safety and rights of participants. All the eCRFs will be routed to the coordinating center, APHM ([name]). Data entry will be performed using REDCap. Quality assurance will be performed from the final database (data manager). The database will be forward to the statistical team (Aix-Marseille Univ, APHM, Clinic Research Platform). The study information of this protocol has been posted on clinicaltrials.gov. The status of this trial is pending: the first inclusion is estimated for September 1st^,^ 2019.

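### CGQL and EQ-5D-5L are measured at baseline, but the stated two-sample tests make no use of that value as a covariate and so give up precision

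*Protocol article*

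**What the plan says.** In the protocol article, the Endpoints section schedules CGQL and EQ-5D-5L "at baseline and 3 and 12 months from continuity restoration (i.e., either IPAA or ileostomy closure". The Data collection and monitoring section confirms that the case report form holds a "baseline QoL assessment, using CGQL and EQ-5D-5 L".

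The Statistical analysis section gives one rule for every continuous secondary outcome: "For the secondary endpoints, quantitative data will be compared using the Student’s t test or Mann-Whitney U test in accordance with the variable distribution". It does not say whether the quality-of-life tests are applied to follow-up values or to changes from baseline.

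The same section names only two kinds of regression model. One is described with the binary primary endpoint: "Logistic regression will be performed to adjust for potential confounding factors". It is given second rank: "The unadjusted analysis will be the primary analysis, and the adjusted analysis will be a complementary analysis". The other is a set of Cox models for survival. Neither suits a continuous quality-of-life score.

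Not every quantitative outcome has a baseline. The pouch score is listed as "functional results assessed by the Cleveland Pouch Functional score (PFS) 3 and 12 months from continuity restoration", without a baseline measurement, and length of stay cannot have one.

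**The concern.** The trial collects a baseline score for two instruments and then names, for the comparison of arms, two tests that cannot use it as a covariate. This is a stated choice, not a gap left open. An analysis plan that followed the article would carry the inefficiency, and one that used ANCOVA would depart from it.

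The choice between a test of means and a test of ranks is also tied to how the data turn out to be distributed. The same instrument could then be summarised by a different quantity at 3 months than at 12.

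What is at stake is the width of the confidence intervals for quality of life. The Discussion presents the effect of the ileostomy on quality of life as one of the trial's new contributions, so precision there has value.

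**Working it through.** **Inputs**
- From the document: allocation "with a 1:1 allocation ratio", and the sample size statement "With the alpha risk and power fixed to 0.05 and 0.80, respectively, 88 patients need to be included in each group, or 176 in total".
- Assumed: two-sided alpha (sidedness is not stated); equal standard deviations at baseline and follow-up; and r, the baseline-to-follow-up correlation, shown over a range because the document gives none.

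**The plan's own figure.** No figure is given for the quality-of-life comparison. The 88 per group belongs to the binary primary endpoint. For 55% vs 30%, two-sided 0.05 and power 0.80, the usual formula gives

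n = [1.960·√(2·0.425·0.575) + 0.842·√(0.55·0.45 + 0.30·0.70)]² / 0.25² = 60.2, so 61 per group (68 with continuity correction).

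The 88 is therefore not reproduced. That is a separate matter: I take 88 per arm as given, and the variance ratios below do not depend on n.

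**Variance of the difference between arms**, with a t test on follow-up values set to 1:
- t test on change from baseline: 2(1 − r)
- ANCOVA with the baseline score: 1 − r²

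The difference between the last two is 2(1 − r) − (1 − r²) = (1 − r)², which is positive for every r below 1. ANCOVA therefore beats the change-score test at every such r, and beats the follow-up test whenever r is not 0. The conclusion does not depend on which reading of the Statistical analysis section is right.

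**Power and equivalent size.** With 88 per arm, a t test on follow-up values has 80% power for a standardised difference of 2.80·√(2/88) = 0.422. For that same difference:

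| r | Change-score variance | ANCOVA variance | Variance saved vs follow-up test | ANCOVA power | Equivalent total, 176/(1 − r²) |
|---|---|---|---|---|---|
| 0 | 2.00 | 1.00 | 0% | 80.0% | 176 |
| 0.2 | 1.60 | 0.96 | 4% | 81.6% | 183 |
| 0.3 | 1.40 | 0.91 | 9% | 83.6% | 193 |
| 0.4 | 1.20 | 0.84 | 16% | 86.4% | 210 |
| 0.5 | 1.00 | 0.75 | 25% | 89.9% | 235 |
| 0.6 | 0.80 | 0.64 | 36% | 93.8% | 275 |

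From r = 0.2 to r = 0.6 the equivalent gain in patients is 1/0.96 = 1.04 to 1/0.64 = 1.56, that is 4% to 56%. These figures credit the baseline score alone. They count neither a gain from the stratification factors nor the small loss of degrees of freedom from fitting them.

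**The case against.** **The sentence is generic and the analysis plan is not shown.** A condensed article may leave quality-of-life modelling to that plan. This would answer a silence, but the article names the unadjusted tests for all quantitative secondary endpoints, so the objection does not remove the point.

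**The correlation may be low.** This stands. According to the Background, subtotal colectomy leaves the patient with an end ileostomy or double-end stoma, so baseline quality of life is reported in a different health state from follow-up with a working pouch. At r = 0.2 the gain is worth about 7 patients (183 against 176). The upper end of the range cannot be presented as expected.

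**Three stronger readings are tempting and are not supported.**
- *A reader might infer that chance baseline differences bias the results.* Under randomised allocation the unadjusted comparison is unbiased, and chance imbalance is already part of its standard error.
- *A reader might infer that a baseline imbalance in utility passes straight into the incremental QALY by a material amount.* The Economic assessment section gives no formula for the QALY and says nothing on baseline utility. If one assumed a trapezoid over 0, 3 and 12 months, baseline would have weight 0.125 year, and an assumed imbalance of 0.03 would enter directly as 0.03 × 0.125 = 0.004. With carry-over to follow-up it would be 0.03 × (0.125 + 0.875r), or 0.012 to 0.020 at r = 0.3 to 0.6. Because all of this rests on an unstated formula, no QALY shift can be claimed.
- *A reader might infer that choosing the rank test leaves the economic analysis without a mean difference.* It does not. That analysis is described separately, and a mean can be computed from patient-level utilities whatever test supplies the p-value.

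**Conclusion.** The point holds as one of efficiency. For CGQL and EQ-5D-5L the stated tests are valid but less precise than a baseline-adjusted analysis, on follow-up values or on changes. Relative to a follow-up t test, the avoidable variance is 4% to 36% for an assumed r of 0.2 to 0.6, small at the lower end and material from about 0.5. It is nil at r = 0. The result rests on r and, for the change-score comparison, on equal standard deviations at the two times. The primary endpoint, the pouch functional score and length of stay are not touched, and no finding of bias or of an error in the QALYs follows.

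**What to change.** For CGQL and EQ-5D-5L only, replace the general rule with a prespecified model: ANCOVA at each follow-up visit, or one mixed model using both visits, with the baseline score and the two stratification factors (BMI group and centre) as covariates. Report the adjusted mean difference between arms with its 95% CI at 3 and at 12 months, and keep the Mann-Whitney test as a sensitivity analysis. With 15 centres and 176 patients there are about 12 per centre (176/15), so the plan should also say how centre enters, for example as a random effect. The existing rule can stay for outcomes without a baseline value.

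The cost is wording in the analysis plan, settled before the data are examined. No new data, visits or patients are needed.
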